### Handling of study dropouts

Each week, participants in intervention arms one and two will be sent an automated e-mail that will contain a reminder to login to their consumption diary, a reminder to work on their modules and a direct link to the Can Reduce login site. If participants do not log in, they will receive a reminder e-mail every three days for the following two weeks. If they do not continue their participation after these reminders, they will be considered to have dropped out of the study. Participants allocated to study arm 1 (chat and self-help) will additionally be invited to the first chat session at least three times over two weeks if they do not respond. In each of these invitations they will be asked to agree to attend two chat sessions on dates suggested by their counselor. If the participants are unable to attend on these dates, they will have the opportunity to suggestion dates to the counselor. This procedure will be repeated until a first chat date has been found. If participants do not show up at the agreed chat date they will be sent new chat dates until a first chat appointment occurs. If participants do not reply after three invitations to schedule chat appointment, they will be considered to have dropped out of the study. The second chat appointment will be scheduled at the end of the first chat session. If participants do not show up for the second session, they will be sent new chat dates twice. Attendance of at least one chat appointment will be required of the participants, otherwise they will be considered to have dropped out. Participants in study arm 1 who discontinue their consumption dairies but proceed with the chat session will not be considered as drop outs and will be included in the study.

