[40], which is a validated and user-friendly self-assessment questionnaire that assesses recent mental distress and self-reported diagnoses of depression; 8) the CLAMES, which is a standardized measure of functional health states that provides a simple, generic measure of health for clinical and economic appraisal. This instrument consists of a descriptive system to measure pain/discomfort, physical functioning, emotional state, fatigue, memory and thinking, social relationships, anxiety, speech, hearing, vision, and use of hands and fingers on four or five levels that range from no problems to extreme problems
[41]. Overall intervention satisfaction will be ascertained on a visual analogue scale from absolutely unsatisfied to absolutely satisfied. Finally, retention will be derived from the last cannabis use input entered into the consumption diary in study arms one and two.

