### Data analysis

Data will be analyzed according to the intention-to-treat principle (ITT). For the ITT analyses, we will apply the multiple imputations procedure (MICE) of STATA, which imputes missing data using all available baseline variables (sociodemographic and health- and cannabis-related variables). Baseline measurements will be compared using t- and Chi-squared tests. Differences between primary and secondary outcome variables between baseline and the follow up points will be tested using generalized estimating equation (GEE) models. GEE is a repeated-measures regression model that takes into account the correlations between the repeated measures from each person
[45]. We will perform logistic GEE analyses for the binary outcome variables and linear GEE analysis for continuous outcome variables. Results from the imputed data set will be cross-checked with the non-imputed data set.

We will conduct additional exploratory regression analyses to determine whether baseline variables predict the severity of cannabis use disorder (CUDIT, SDS), cannabis craving (CCS-7), cannabis withdrawal (CWS), reduced psychiatric symptoms (MHI-5), and treatment retention. For these analyses, we will use linear, multinomial, or binary regression models depending on the scale of the outcome measure.

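### Study dropout is defined by non-adherence in the active arms only, which conflicts with intention-to-treat and with the open 3-month invitation

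*Protocol article*

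**What the plan says.** The protocol article, under Handling of study dropouts, gives three routes out of the trial, all based on behaviour after randomisation:

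- **No log-in (arms 1 and 2).** The weekly prompt is confined to the active arms: "Each week, participants in intervention arms one and two will be sent an automated e-mail". After two weeks of further reminders, "If they do not continue their participation after these reminders, they will be considered to have dropped out of the study".
- **No reply to chat invitations (arm 1).** "If participants do not reply after three invitations to schedule chat appointment, they will be considered to have dropped out of the study".
- **No chat attended (arm 1).** "Attendance of at least one chat appointment will be required of the participants, otherwise they will be considered to have dropped out".

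The section closes with an exception. Arm 1 participants who stop the diary but continue with chat "will not be considered as drop outs and will be included in the study". It gives no rule for arm 3.

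Under Data analysis the plan is different: "Data will be analyzed according to the intention-to-treat principle (ITT"). Missing data are handled by multiple imputation, "which imputes missing data using all available baseline variables (sociodemographic and health- and cannabis-related variables"), with a cross-check on the non-imputed data. Trial flow says that participants are invited to the 3-month assessment (t2), with a 40 Euro incentive, and sets no condition on arm, log-ins or chat attendance. The Discussion adds that all missing values will be imputed.

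**The concern.** Leaving an intervention and leaving a trial are different events. Intention-to-treat needs outcomes from people who stop the intervention, because they belong to the randomised comparison. Here, stopping the intervention is itself defined as leaving the study.

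The definition also differs by arm. An arm 1 participant who works through all the self-help but never chats is a dropout, while the same use of the self-help in arm 2 is not. An arm 2 participant who abandons the diary is a dropout, while an arm 1 participant who does so but chats is not. A waiting-list participant cannot drop out by any of these routes.

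If trial staff acted on this wording, t2 outcomes would be missing according to engagement, in a different pattern in each arm. That would affect the primary outcome in all three hypotheses. Outcomes not collected at 3 months cannot be recovered later.

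**Working it through.** **1. The sections side by side**

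| Question | Handling of study dropouts | Elsewhere in the protocol |
|---|---|---|
| Who leaves the study? | Non-adherers in arms 1 and 2 | Consent procedure: those who choose to withdraw |
| Who is in the analysis? | Last sentence: a group that is not classed as dropouts is included | Data analysis: intention-to-treat |
| Who is invited to t2? | Not stated | Trial flow: participants, without restriction |
| Rule for arm 3? | None | None |

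The closing exception is needed only if dropouts would otherwise not be included. Other sections show what being outside the study means in this protocol. Under Baseline assessment, people not in the study have no assessments or compensation. Under Consent procedure, withdrawal costs further compensation, and the only compensation described is the 40 Euro at t2. Two details add to the exposure. Table 1, footnote 2, derives quantity of use from the consumption diary. The telephone fallback at 3 months is described only in the waiting-list paragraph of Study interventions.

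**2. Would imputation repair it?**

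The stated imputation model uses baseline variables. Engagement arises after randomisation and is not named in it. If t2 is not collected from non-engagers, their values are modelled from engaged participants with similar baselines. Any prognostic difference that baseline does not explain then remains in the arm mean. The non-imputed cross-check is exposed to the whole difference.

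**3. Illustration of size**

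*The plan's figure.* The sample size section gives 89 per arm and 267 in total (f = 0.15, 80% power, α = 5%). A two-group, two-time-point interaction test with a correlation of 0 between time points (an assumption, as none is stated) has λ = f² × N × m / (1 − ρ) = 0.0225 × 178 × 2 / 1 = 8.01 on 1 and 176 degrees of freedom. That reproduces 89 per arm, and 3 × 89 = 267. The point made here needs only the 89.

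*Assumptions, not in the documents.* There is no true effect. A share q of one active arm is excluded and the waiting list is complete. Engaged participants do better than non-engaged by D standard deviations whatever the treatment. The analysis is complete-case.

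- Spurious difference: b = q × D, because the engaged mean exceeds the whole-arm mean by that amount.
- SE = √(1/(89(1 − q)) + 1/89).
- Two-sided type I error = 1 − Φ(1.96 − b/SE) + Φ(−1.96 − b/SE).

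Worked case, q = 0.3 and D = 0.3: b = 0.09; SE = √(1/62.3 + 1/89) = 0.165; b/SE = 0.545; error = 8.5%.

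| D (SD) | q = 10% | q = 30% | q = 50% |
|---|---|---|---|
| 0.1 | b = 0.01, 5.0% | b = 0.03, 5.4% | b = 0.05, 5.9% |
| 0.3 | b = 0.03, 5.4% | b = 0.09, 8.5% | b = 0.15, 12.9% |
| 0.5 | b = 0.05, 6.2% | b = 0.15, 14.8% | b = 0.25, 27.5% |

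If every randomised participant is followed up and analysed as allocated, b = 0.

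**The case against.** The strongest reply is that the dropout section only labels people for flow reporting and ends the reminders, while the Data analysis section governs who is analysed. No sentence says that dropouts are removed from the analysis or denied the t2 invitation. Imputation of all missing values is planned, and nothing says that observed t2 values would be discarded or overwritten. A condensed article may also leave follow-up of discontinuers to the full protocol.

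Much of this stands. A reader might infer that the trial will exclude non-adherers from its primary analysis; the documents do not establish that. The table above models a complete-case exclusion that the plan does not describe as its main analysis, and at its low end there is almost no inflation.

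A reader might also infer a bias in favour of arm 1. That is not supported either. The Discussion expects attrition to be higher on the waiting list. Between arms 1 and 2, the arm 1 rule is stricter on chat but more lenient on the diary.

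Nor is the retention outcome defined inconsistently: "retention will be derived from the last cannabis use input entered into the consumption diary in study arms one and two". That is one definition for both active arms, and it measures something other than study dropout.

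The reply does not remove the conflict. The article does not merely omit a detail. It states a rule that ends study participation for non-adherence and ties inclusion in the study to it.

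**Conclusion.** The dropout section conflicts with the intention-to-treat analysis and with the unrestricted t2 invitation, and the sections must be reconciled. The finding is conditional: selection on engagement follows if the dropout wording is applied literally, and imputation from baseline variables alone would not then remove the bias. Neither the size nor the net direction of that bias can be read from the documents. The range of about 5% to 27.5% for type I error rests wholly on the assumed exclusion shares, the assumed prognostic differences and a complete-case analysis. Because uncollected outcomes cannot be restored, the wording should be settled before 3-month follow-up.

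**What to change.** - Under Handling of study dropouts, describe all these cases as having discontinued the intervention. Remove the statements that they have left the study, and the closing sentence that makes inclusion depend on adherence.
- State that every randomised participant receives the t2 invitation, its reminders and the 40 Euro offer, whatever their log-ins or chat attendance, and that only withdrawal of consent ends follow-up.
- State under Data analysis that all participants are analysed in their allocated arm, that observed t2 values are used wherever they exist, and that imputation is confined to values that are truly missing.

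The retention measure needs no change on this account. The cost is a few sentences, some further automated e-mails, and 40 Euro for each additional participant who completes t2.

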### Data analysis

Data will be analyzed according to the intention-to-treat principle (ITT). For the ITT analyses, we will apply the multiple imputations procedure (MICE) of STATA, which imputes missing data using all available baseline variables (sociodemographic and health- and cannabis-related variables). Baseline measurements will be compared using t- and Chi-squared tests. Differences between primary and secondary outcome variables between baseline and the follow up points will be tested using generalized estimating equation (GEE) models. GEE is a repeated-measures regression model that takes into account the correlations between the repeated measures from each person
[45]. We will perform logistic GEE analyses for the binary outcome variables and linear GEE analysis for continuous outcome variables. Results from the imputed data set will be cross-checked with the non-imputed data set.

We will conduct additional exploratory regression analyses to determine whether baseline variables predict the severity of cannabis use disorder (CUDIT, SDS), cannabis craving (CCS-7), cannabis withdrawal (CWS), reduced psychiatric symptoms (MHI-5), and treatment retention. For these analyses, we will use linear, multinomial, or binary regression models depending on the scale of the outcome measure.

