### Estimation of the expected effect sizes and sample size

Based on results of the study of Rooke and colleagues
[23], we expect small to medium effect sizes for the reduction of the quantity of cannabis used and the frequency of cannabis use between study arm 2 (web-based self-help without chat counseling) and study arm 3 (waiting list control) of at least 0.15 (Cohen’s f) between t0 and t2. Assuming that the study arm 1 (web-based self-help with chat counseling) will result in a larger Cohen’s f, we rely on the aforementioned comparison (arm 2 vs. arm 3) for sample size estimation. A sample size of n = 89 in each study group would have 80% power (F-test, α = 5%) to detect this difference based calculations performed with the G-Power software. Thus, we aim to recruit a total of 267 participants.

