### Randomization and allocation

Once participants have completed their baseline assessment, they will be randomized by a computer program in a 1:1:1 ratio to 1 of 3 “parallel” groups, and this assignment will be automatically registered in the background database. As we offer full transparency on the three groups, we expect a certain risk that some might try to circumvent their assignment by registering another account in hope to end up in a different group. In case a participant surmounts the administrative hurdle, he nevertheless will be assigned to the same group for a certain amount of time, based on his IP-address.

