Finally, another potential problem for this trial is the expected high attrition rates at the end of online therapy and at the follow up; this attrition will also likely be higher in the waiting list control group. We will address this issue in three ways: 1) all participants must invest approximately 20 minutes for the baseline assessment, which will select more motivated participants and prevent the participation of un-motivated participants; 2) participation in the 3-month follow up assessment will be compensated by a 40 Euro incentive (an online voucher or an online charitable donation); 3) all missing values in the final data set will be imputed, a promising approach that, as shown by our Dutch colleagues, has become increasingly important in e-health research
[49].

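### The stated imputation predictors are baseline variables without randomised arm; followed as written, this attenuates every comparison with the waiting list

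*Protocol article*

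**What the plan says.** The Data analysis section of the protocol article says that the ITT analysis uses the MICE procedure in STATA, "which imputes missing data using all available baseline variables (sociodemographic and health- and cannabis-related variables"). Linear or logistic GEE models follow. The only check described is this: "Results from the imputed data set will be cross-checked with the non-imputed data set".

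The Discussion expects high attrition and adds that "this attrition will also likely be higher in the waiting list control group". One of its three remedies is that "all missing values in the final data set will be imputed".

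The sample size section assumes an effect for arm 2 versus arm 3 "of at least 0.15 (Cohen’s f) between t0 and t2" and derives 89 per group for 80% power at α = 5%. It concludes: "Thus, we aim to recruit a total of 267 participants". That is 3 × 89, with no allowance for dropout. Allocation is 1:1:1.

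Table 1 marks quantity and frequency of use at weeks 1, 3 and 6, and SDS at week 6, without limiting them to certain arms. The sections on trial flow and on study dropouts describe diary prompts for arms 1 and 2 only.

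**The concern.** An imputation model should contain at least the variables of the analysis it feeds. The main hypotheses compare arms, so arm has to be in the analysis model. If it is absent from the imputation model, missing 3-month values are drawn from a regression pooled over arms. Participants imputed in an active arm and on the waiting list then have the same expected outcome given baseline. Mixing them with the observed values dilutes the contrast.

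The ITT tests of hypotheses 1 and 2 are at stake. The plan expects high attrition, relies on imputation to deal with it and has no spare sample size.

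**Working it through.** **Inputs.** From the document: f = 0.15, 89 per group, α = 5%, power 80%, 1:1:1 allocation. The missing share at 3 months is not given for this trial. The nearest figure is the 54% and 52% retention that the Background cites for the Australian trial, which is also the source of the effect size. I therefore use an assumed range of 10% to 50%.

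**Step 1: reproduce the stated sample size.** A repeated-measures F-test with 2 groups, 2 time points and correlation 0 has noncentrality λ = f² × N × 2. With N = 178, λ = 0.0225 × 356 = 8.01 and power is 0.804. N = 178 is the smallest N that reaches 80%, so 89 per group is reproduced. The correlation is not stated; zero is the value that fits. I keep this basis so that only f changes below.

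**Step 2: effect of leaving arm out.** Let arm k have mean benefit μₖ and retention rₖ, with missingness unrelated to outcome within arm. Without arm, imputed values centre on the pooled observed mean μ̄ = Σrₖμₖ / Σrₖ. The completed-data contrast of arms j and k is

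rⱼ(μⱼ − μ̄) − rₖ(μₖ − μ̄).

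With equal retention r = 1 − m this becomes (1 − m)(μⱼ − μₖ).

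**Step 3: equal missingness on the protocol's own basis.**

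| m | f(1 − m) | λ = f² × 356 | Power, arm omitted | Power, f = 0.15 with N = 178(1 − m) |
|---|---|---|---|---|
| 0 | 0.15 | 8.01 | 0.80 | 0.80 |
| 10% | 0.135 | 6.49 | 0.72 | 0.76 |
| 20% | 0.12 | 5.13 | 0.62 | 0.71 |
| 35% | 0.0975 | 3.38 | 0.45 | 0.62 |
| 50% | 0.075 | 2.00 | 0.29 | 0.51 |

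The last column approximates an imputation that includes arm. Missing data cost power in any case, so only the gap between the last two columns is due to the omission.

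**Step 4: unequal missingness.** Take retention 0.7/0.7/0.5 and assumed benefits of 0.4, 0.3 and 0 SD.

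- μ̄ = (0.28 + 0.21 + 0)/1.9 = 0.258.
- Arm 2 versus waiting list: 0.7 × (0.3 − 0.258) + 0.5 × 0.258 = 0.158.
- Factor: 0.158/0.3 = 0.53, whereas 1 minus the average missing share would be 0.63 over three arms and 0.60 over these two.

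For arm 1 versus arm 2 with no true difference (0.3, 0.3, 0) and retention 0.8/0.5/0.6:

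- μ̄ = 0.39/1.9 = 0.205.
- Contrast: (0.8 − 0.5) × (0.3 − 0.205) ≈ 0.03 SD in favour of arm 1. The sign reverses if arm 2 is the better retained.

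**Step 5: simulation.** Set-up: 3 × 89 participants, SD 1, baseline correlation 0.5, benefits 0.4/0.3/0, 10 imputations, 600 runs, with a baseline-adjusted linear model standing in for the GEE. Interim use was available for only some of those missing at 3 months. Cells show the arm 2 versus waiting-list estimate (truth 0.30) and the rejection rate.

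| Missing (arms 1/2/3) | Baseline only | + arm | + interim use, no arm | + both |
|---|---|---|---|---|
| 20/20/20% | 0.242; 0.37 | 0.291; 0.50 | 0.254; 0.41 | 0.302; 0.56 |
| 47/47/47% | 0.156; 0.04 | 0.286; 0.34 | 0.190; 0.12 | 0.296; 0.40 |
| 30/30/50% | 0.159; 0.09 | 0.300; 0.39 | 0.197; 0.16 | 0.299; 0.45 |

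Arm alone restores 95% to 100% of the effect. Interim use without arm does not. The rejection rates rest on a different basis from Step 3 and should be compared only within this table.

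**The case against.** The strongest case against is that this is a condensed article. The word only does not appear, arm is not said to be excluded, and a fuller specification may exist elsewhere. Chained equations normally also condition on the other incomplete variables, so interim use may already be in the model. The GEE sentence does not name arm either, yet nobody doubts that it will be there.

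Part of this stands: exclusion is inferred, and the authors may have intended to include arm. But the sentence is not silent on the model. It states a predictor set and lists its classes, and arm fits none of them. The GEE sentence lists no predictors, and the hypotheses cannot be tested without arm. If interim use is in the model but arm is not, Step 5 still shows only 63% of the effect at 47% missing.

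A second objection is that missingness may be modest. The 3-month assessment is compensated with 40 Euro, and the waiting list can be reached by telephone. This is fair, and it is why a range is given: at 20% missing, about four fifths of the effect remains.

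Third, the comparison with non-imputed data could expose the shrinkage. It could, but it does not correct the ITT estimate, and the text does not say which result prevails.

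**Conclusion.** The point holds. As written, the predictor list omits randomised arm, and following it attenuates each comparison with the waiting list. The factor is (1 − m) under equal missingness. On the protocol's own basis, power then falls from 0.80 to between 0.72 (10% missing) and 0.29 (50% missing), part of which would be lost even with arm included. These figures assume missingness unrelated to outcome within arm, the zero correlation that reproduces 89 per group, and a missing share that the document does not state.

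Several stronger readings are tempting, but the document does not support them:

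- **Omitting week 1, 3 and 6 use also pulls the effect to zero.** It does not in itself. It costs precision and makes the missing-at-random assumption less plausible; bias follows if dropout depends on interim use.
- **The effect will be halved.** That needs about half the data missing, a figure borrowed from another trial.
- **Shrinkage is always proportional to the missing share and towards zero.** Proportionality needs equal missingness, and the arm 1 versus arm 2 contrast can move either way.
- **Interim data exist for everyone.** Table 1 sets no arm limit, but the prompts are described for arms 1 and 2 only.
- **The lack of a delta-adjusted analysis is an error.** Such an analysis is optional.

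**What to change.** 1. State in the Data analysis section that randomised arm is in the imputation model, or that imputation is done separately by arm. Arm is known for every randomised participant, so this costs one sentence and no new data.
2. Add post-baseline quantity and frequency of use, and week-6 SDS, to the imputation model where they are collected in all arms. The gain is precision and a more plausible missing-at-random assumption.
3. Clarify whether the waiting list provides data at weeks 1, 3 and 6, reconciling Table 1 with the sections on trial flow and study dropouts. If it does not, item 2 is limited accordingly.

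A delta-adjusted sensitivity analysis could be added if the team wishes, but the correction does not depend on it.

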^1)^ Additional retrospective cost-relevant information directly or indirectly related to cannabis use will be collected by the CLAMES to conduct cost-effectiveness and cost-utility analyses.

^2)^ 7-day point prevalences of the quantity (in common standard joints) and frequency (the number of days on which cannabis is used) of cannabis use will be derived from the consumption diary assessed daily using data from the last 7 days.

Moreover, the following secondary outcome instruments will be applied: 1) cannabis consumption days per week according to the consumption diary; 2) the Cannabis Use Disorders Identification Test (CUDIT), which is a 10-item questionnaire
[33] that was constructed by adapting the Alcohol Use Disorders Identification Test (AUDIT
[34]). To cover the length of the trial length, this instrument will be adapted to focus on the last 3 months in its planned assessments (baseline and 3-month follow up); 3) The Severity of Dependence Scale (SDS), which is a 5-item questionnaire that measures the severity of cannabis dependence. Each of the five items is scored on a 4-point scale (0–3). The total score is obtained through the addition of the ratings on all 5 items. High scores indicate high levels of dependency
[35]; 4) The Cannabis Withdrawal Scale (CWS)
[36], which is a 26-item questionnaire containing statements that describe cannabis withdrawal symptoms within the last 24 hours on 11-point scales (0–10); 5) The Cannabis Craving Symptoms questionnaire (CCS-7), which is a 7-item questionnaire
[37] derived from the Marijuana Craving Questionnaire
[38]. Each item is rated on a 7-point-scale (1–7); 6) the “Fragebogen Substanzanamnese” (FDA), which is a questionnaire that ascertains the number of years of consumption over the lifetime, the past month’s consumption, and the manner of consumption for DSM-IV/ICD-10 substances of abuse. This measure was derived from the Europe ASI
[39]; 7) the short version of the Mental Health Inventory (MHI-5)

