Some participants may want to reduce their cannabis use only marginally and might reach their aims in the first weeks of the intervention, which might result in discontinuation of participation in the online self-help intervention. Therefore, we will recommend that participants reduce their cannabis by at least 20 to 30 percent in the first week of the intervention and continue with this strategy in subsequent weeks if they succeed. For participants who do not succeed, we will recommend that they create more modest goals until their final aim is received. Participants receiving chat counseling will additionally be motivated by their counselors to avoid setting their goals too low.

During the online implementation of the consumption diary of the web-based self-help intervention, pilot participants stressed the importance of the definition of common standard joints as the most appropriate measure for the consumption diary. On the one hand, the established cannabis meter pictures from the global drug survey website facilitated the pilot participants’ entry of their cannabis use, and, on the other hand, they felt more motivated by a tailored photograph than a written instruction. In our opinion, this is the most effective method to collect appropriate quantity measures, especially from cannabis users who use cannabis several times a day. However, as this is the first time this kind of quantity measure will be used in a randomized controlled trial, we will also rely on the number of days per week that cannabis is used.

One specific problem involves the online implementation of informed consent. As in previous research
[21], we will rely on participants to click on a field on the informed consent page and submit the consent with a submission button. Thus, we must trust that the participants have read and understood the study information and that they are at least 18 years old. However, as we followed the recommendations of
[47] and
[48] regarding the best implantation of online informed consent procedures, we expect that the participants will read the study information in full and provide informed consent.

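### The one stated missing-data check, imputed against non-imputed data, cannot detect or bound dropout that depends on the unseen 3-month quantity

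*Protocol article*

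**What the plan says.** All references are to the protocol article.

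- **Data analysis.** The analysis is intention-to-treat. The MICE procedure "imputes missing data using all available baseline variables (sociodemographic and health- and cannabis-related variables"). Trial arm and the diary values at weeks 1, 3 and 6 are not named as predictors. Changes in outcomes "will be tested using generalized estimating equation (GEE) models", with no weighting mentioned. The single check on missing data is: "Results from the imputed data set will be cross-checked with the non-imputed data set".
- **Discussion, on attrition.** The article says that "another potential problem for this trial is the expected high attrition rates at the end of online therapy and at the follow up", and that "this attrition will also likely be higher in the waiting list control group". Imputing all missing values is listed as one of three responses, beside the length of the baseline assessment and the 40 Euro incentive.
- **Discussion, on early success.** Some participants who want only a small reduction "might reach their aims in the first weeks of the intervention, which might result in discontinuation of participation in the online self-help intervention".
- **Handling of study dropouts.** For arms 1 and 2, on persistent failure to log in: "If they do not continue their participation after these reminders, they will be considered to have dropped out of the study".
- **Measurement instruments, notes to Table 1.** Quantity and frequency of use "will be derived from the consumption diary assessed daily using data from the last 7 days".

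**The concern.** Read together, these sections describe a route by which the outcome itself could cause the outcome to be missing. A participant in arm 1 or 2 succeeds, stops logging in, is classed as a dropout, and no longer fills in the diary from which the primary outcome is derived. The opposite route, in which participants who fail give up, is equally open, although the article does not mention it.

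Imputing from baseline variables assumes that, given those variables, people who are missing resemble people who stay. Unweighted GEE on the available data needs an assumption at least as strong about the unseen values. A comparison of two analyses that both exclude outcome-related dropout cannot tell the reader whether it occurred or how much it matters. The risk is that agreement is later presented as reassurance on the very point that was not examined, in a trial that expects high attrition and whose positive result would lead to adoption on a national portal.

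**Working it through.** **1. The plan's effect size, as a yardstick.** Estimation of the expected effect sizes and sample size gives Cohen's f = 0.15, 80% power, α = 5% and 89 per arm. A repeated-measures F-test with 2 groups, 2 time points and correlation 0 has noncentrality f² × N × 2. At N = 178 this is 0.0225 × 178 × 2 = 8.01, with power 0.804. The smallest N is 177, that is 89 per arm, so the figure is reproduced. With correlation 0, two tests give the same number:
- a between-group test, which implies d = 2f = 0.30 SD;
- a group-by-time test, which implies a difference in change of 0.60 SD.

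A one-way two-group test would need N = 351. The planned effect is therefore 0.30 or 0.60 SD, depending on the reading.

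**2. Share missing (assumption).** The article gives no expected figure. The Australian trial cited in the Background retained 54% and 52% at 3 months, so 46% and 48% were missing, about 47%. I use 30% to 47%.

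**3. Shift in the effect.** Let the effect be active minus waiting list in weekly quantity, so that negative means benefit. Let π be the share missing in an arm, and δ the mean of the dropouts minus the mean imputed for them. Then

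estimate − truth = π(waiting list) × δ(waiting list) − π(active) × δ(active).

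With |δ| = 0.3 SD in the active arm only:
- 30% missing: 0.30 × 0.3 = 0.09 SD
- 47% missing: 0.47 × 0.3 = 0.14 SD

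If achievers leave, δ(active) is negative and benefit is understated. If non-responders leave, it is positive and benefit is overstated.

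Shift in the active arm that cancels the planned effect entirely:
- effect 0.30 SD: 0.30/0.47 = 0.64 SD; 0.30/0.30 = 1.0 SD
- effect 0.60 SD: 0.60/0.47 = 1.28 SD; 0.60/0.30 = 2.0 SD

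**4. Does the stated check react? Baseline and one outcome.** Simulation with 89 per arm, about 46% missing, true effect 0, arm in the imputation model, and baseline-adjusted regression standing in for the GEE. Dropout in the active arm depends on the 3-month outcome.
- Achievers leave: complete case +0.283, imputed +0.283; the true null is rejected in 39% and 38% of runs.
- Poor responders leave: −0.282 and −0.285; rejected in 37% and 36%.
- The mean absolute gap between the two analyses is about 0.03 SD, the same as when data are missing completely at random.

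**5. Does it react with the diary time points in the GEE?** Simulation with five time points, true effect −0.30, baseline-only imputation, exchangeable GEE on the non-imputed data.
- Dropout depends on observed week-3 use: imputed −0.17, GEE −0.31; gap 0.14.
- Dropout depends on the 3-month outcome: imputed +0.16, GEE +0.07; gap 0.16 − 0.07 = 0.09.

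The gap is larger where the GEE is close to the truth than where both analyses are badly biased. Its size is therefore no guide to outcome-related dropout. The decimals depend on the dropout model chosen; the pattern is what matters.

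**6. Another source of disagreement.** If arm is left out of the imputation model, a true −0.30 shrinks to about −0.16 with no outcome-related dropout at all. A discrepancy could then reflect the imputation model alone.

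**The case against.** **Scope.** Tipping-point analyses usually belong in a SAP, and one may exist. The article does not say that its cross-check is the only check, or that agreement would prove robustness. This stands as a limit on tone. The article does, however, choose this check itself and lists imputation among its answers to attrition, so the point concerns what is fixed here and not detail left out.

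**Agreement is not automatic.** A reader might infer that the two analyses must agree. That holds in the one-outcome setting of step 4, but not if the GEE uses the interim diary values that the stated imputation omits. In step 5 the check diverged when dropout followed week-3 use. Since the Discussion speaks of aims reached in the first weeks, part of that dropout may depend on observed diary values. This stands. It rests on the GEE including those time points with an exchangeable working correlation, which the article does not state, and it does not help where dropout depends on the unseen 3-month value.

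**Higher waiting-list attrition.** A reader might infer that this alone breaks the assumption. It does not. With 35% versus 55% missing by arm, a true effect of −0.31 SD and arm in the imputation model, all analyses averaged −0.31.

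**Early achievers.** The passage is hedged and concerns leaving the self-help intervention, not declining the 3-month assessment. That assessment has its own e-mail invitation and a 40 Euro incentive, and the article adds goal-setting advice to limit early stopping. All of this stands. Some outcomes may be recovered, and the passage raises a possibility; it does not forecast missing outcomes.

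**Conclusion.** The concern holds in this form: the stated comparison can neither detect nor bound dropout related to the unseen 3-month quantity, and neither agreement nor disagreement between the two analyses measures it. The article itself raises this kind of dropout as a possibility.

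Assuming 30% to 47% missing in an arm and a 0.3 SD difference between dropouts and their imputed values, the effect moves by about 0.09 to 0.14 SD. At 47% missing, 0.14 SD is about half of a planned 0.30 SD, or about a quarter of 0.60 SD. The share missing and the size of the shift are both assumptions.

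A reader might go further and infer that a positive finding could come entirely from who dropped out. The documents do not support that. The direction they suggest, achievers leaving the active arms, understates benefit. Cancelling the planned effect would need a shift of at least 0.64 SD in the opposite direction, which no section predicts. The primary analysis is not invalidated; it lacks an informative sensitivity analysis, which should be added.

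**What to change.** Keep the planned MICE analysis and the non-imputed analysis. Add, in the SAP or the Data analysis section:

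- delta-adjusted multiple imputation, shifting the imputed 3-month quantity separately by arm over a stated grid in both directions, for example −0.5 to +0.5 SD. The grid should widen if needed to reach the tipping point: step 3 shows that full cancellation of the planned effect lies beyond 0.5 SD, although statistical significance may be lost sooner;
- a report of the shift at which the conclusions for hypotheses 1 and 2 change;
- a statement that agreement with the non-imputed result will not be cited as evidence of robustness to outcome-related dropout.

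Cost: a few more runs of an imputation that is already planned, and a short addition to the text. The downside is that the conclusion may have to be stated as conditional on the dropout assumption.
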